#### Sample Size

A sample size of between 24 and 50 is considered reasonable in a feasibility study, to be able to estimate a participation rate in anticipation of a full trial (57, 58). Informed by this, the target recruitment for this feasibility trial will be *N* = 80, allowing for a 20% loss to follow-up rate and for at least 64 participants to complete the study during the COVID-19. The sample size is projected to provide enough numbers to be able to estimate the likely efficacy and acceptability of the training intervention to inform the design of a future RCT.

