#### Randomization

The randomization will be performed by an independent researcher not connected with either participant recruitment or data collection, using a 1:1 ratio as per a computer-generated randomization schedule using randomly permuted block sizes by randomization.com. All eligible participants who give written informed consent will be randomly allocated to either the intervention or control arm of the trial. Due to the nature of the study, only the researcher collecting/analyzing the data from trial participants can be masked to the randomization.

As a check on blindness, the researcher will be asked to guess the group allocation of trial participants after they have completed each final follow-up assessment. Unmasking will not occur until databases are closed and the main analysis has been completed.

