### Statistical Data Analysis

Since this is a feasibility study and is not testing hypotheses regarding effectiveness of PFA training intervention, inferential statistics will not be employed. The primary objectives will be addressed via generating estimates of dispersion and central tendency (i.e., proportions, means, SDs, etc.). The acceptable levels of eligibility and enrolment will be a 90% or greater screening eligibility rate for frontline healthcare workers referred to the study. A recruitment rate is expected of 15 trainees per week and the target sample size would therefore be achieved in 6 weeks. The acceptable proportion of enrolled trainees who complete all the training sessions will be 80% or greater, given that there's 18% dropout rate of participants in PFA training cluster RCT (23). The feasibility of collecting quantitative outcome data includes (1) <20% missing data at the group level for each time point and (2) generating estimates of effect and variability related to by the independent research facilitator. Quantitative secondary objectives will be addressed via generating bivariate correlations and regression coefficients for the selected measures. Correlations between the baseline and follow-up will be estimated for continuous outcomes. Measures will be examined for multi-collinearity, as well as any needed transformation due to unfavorable skewness and kurtosis (72, 73). Appropriate 95% confidence intervals will be reported, with differences deemed significant at the 5% level.

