This study has several strengths. First, to our knowledge, this is the first rigorous evaluation of a systematically adapted PFA training intervention for use by frontline healthcare workers which could help to decide the larger follow-on studies of this low-intensity capacity-building programme. Second, as a feasibility-controlled trial combined with a process evaluation, the combination of data regarding retention rate, the ability of the training program to lead to changes in the secondary objectives of interest (i.e., increased preparedness and self-efficacy, reduced burn-out, and secondary traumatic stress, etc.) gained will shape the design and inform a sample size calculation for a future trial. Experience from the training practice will generate a rich and comprehensive understanding of how PFA training might be delivered in the context of a frontline health service and so potentially widen its application to Chinese population. Third, considering that the sample setting has the combing role of emergency response and regular health service in frontline healthcare context, it may contribute to enhance the understanding of its relevance and applicability of findings in different regions, especially in non-disaster frontline settings. Given the overall aim of developing preventive strategies to improve mental health crisis preparedness for frontline healthcare workers, it is consistent with objectives of addressing frontline challenge in public mental health during complex emergencies (81).

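### The Sample Size section says 80 participants suffice to estimate likely efficacy; 32 completers per arm leave about ±0.49 SD, and the Discussion lets that noisy effect inform the main-trial sample size

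*Protocol article*

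**What the plan says.** The Sample Size section starts from a literature range: "A sample size of between 24 and 50 is considered reasonable in a feasibility study, to be able to estimate a participation rate". It continues "Informed by this, the target recruitment for this feasibility trial will be" 80, "allowing for a 20% loss to follow-up rate and for at least 64 participants to complete the study". It then gives the number a purpose: "The sample size is projected to provide enough numbers to be able to estimate the likely efficacy and acceptability of the training intervention". It states no effect size, SD, power or precision, and does not say whether 24-50 is per arm or in total. The Randomization section fixes equal allocation, "using a 1:1 ratio as per a computer-generated randomization schedule".

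The article describes the input to the later trial's sample size in two ways. Objectives, and the feasibility-trial paragraph under Design, name the variability of participant outcomes. The Discussion lists retention together with the training's ability to change the secondary outcomes, and says the data "gained will shape the design and inform a sample size calculation for a future trial".

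Statistical Data Analysis says that hypotheses about effectiveness are not tested. Among the criteria for feasible outcome collection it lists "generating estimates of effect and variability".

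**The concern.** A range justified for estimating a participation rate is followed by a claim that the resulting size can estimate efficacy. A rate and a between-arm difference in means make very different demands on sample size, and nothing in the section connects them.

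The claim matters because of the Discussion sentence. If the observed difference becomes an input to the main-trial calculation, its sampling error passes into that trial's size. Required size varies with the inverse square of the effect, so a modest overestimate gives a trial far too small and a modest underestimate gives one far too large.

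**Working it through.** **Inputs.** 80 recruited, 20% loss, 64 completers and the 24-50 range (Sample Size); 1:1 allocation (Randomization), hence 40 randomised and 32 completing per arm; training groups of up to 20 (the Introduction's section on the Preparing Me program). Assumed: two-sided 5%, 80% power, and true standardised differences d of 0.2, 0.3 and 0.5.

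**1. The plan's own figure.** 64 / (1 - 0.20) = 80. It reproduces exactly.

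**2. Link to the cited range.**
- Read as a total: 24/0.8 = 30 and 50/0.8 = 62.5, so 30 to 63. Both 80 recruited and 64 completers lie above their respective ranges.
- Read per arm: 48/0.8 = 60 and 100/0.8 = 125. Here 80 lies inside, as do 32 completers per arm within 24-50.

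Neither reading yields 64 or 80 specifically. The link is unexplained rather than wrong.

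**3. Precision of an efficacy estimate.** SE = SD × √(2/32) = 0.25 SD. The half-width is 1.96 × 0.25 = 0.49 SD (0.50 with the t quantile).

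Main-trial size per arm is 2 × ((1.96 + 0.84)/d)², rounded up.

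| d | 95% CI if d is observed | Power with 32 per arm if d is true | Main-trial n per arm if d is true |
|---|---|---|---|
| 0.2 | -0.29 to 0.69 | 12% | 393 |
| 0.3 | -0.19 to 0.79 | 22% | 175 |
| 0.5 | 0.01 to 0.99 | 52% | 63 |

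Every interval contains all three effects. The difference detectable with 80% power is (1.96 + 0.84) × 0.25 = 0.70 SD.

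**4. Clustering.** Suppose groups of 20 keep 16 completers (20 × 0.8), in both arms, with an assumed intraclass correlation (ICC) of 0.01 to 0.05. The design effect is 1 + 15 × ICC = 1.15 to 1.75, and the half-width becomes 0.49 × √1.15 = 0.53 to 0.49 × √1.75 = 0.65 SD.

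**5. Sizing the main trial on the observed effect.** In a simulation, observed effects were drawn from a normal distribution with SE 0.25.
- True d = 0.3 (175 per arm needed): among pilots observing more than 0.05 SD, the middle 80% of calculated sizes ran from 39 to 1003 per arm. Of all pilots, about half gave too small a trial, about 30% gave one with true power below 50%, and 11.5% showed no positive effect.
- True d = 0.5 (63 needed): the middle 80% ran from 24 to 324 per arm.

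**6. What 80 participants do support.**
- An 80% rate overall: 1.96 × √(0.8 × 0.2/80) = 8.8 points. The Wilson interval for 64/80 is 70% to 87%.
- An 80% rate per arm: 1.96 × √(0.8 × 0.2/40) = 12.4 points.
- Pooled SD on 62 degrees of freedom: the chi-square limits are 0.85 to 1.21 times the estimate, about -15%/+21%.

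**The case against.** The strongest reply is that this is loose wording. The one calculation in the section is right, and the text says the target was informed by the range, not computed from it. If the range is per arm, 32 completers sit inside it. The objectives name variability as what feeds the later trial, and 64 completers serve that aim. All of this stands.

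Three stronger readings are tempting and are not supported:
- A reader might infer that Statistical Data Analysis carries the observed effect into the main-trial sample size, or declares effectiveness outside the study. It does neither. The effect estimates appear there as part of showing that outcome data can be collected, and only hypothesis testing of effectiveness is ruled out. An estimate with a confidence interval is compatible with that.
- A reader might infer that a poor pilot effect would lead to the main trial being abandoned. Conclusions ties progression to 80% retention, and no rule uses the observed effect.
- A reader might infer that the main trial will be mis-sized. The Discussion names change and retention jointly as informing the calculation, and does not say that the observed effect becomes the target difference.

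Baseline adjustment would narrow the interval by √(1 - r²), where r is the baseline-to-follow-up correlation, which the article does not give. Getting from 0.49 to 0.15 SD, half the gap between 0.2 and 0.5, needs √(1 - r²) = 0.15/0.49 = 0.31, so r of about 0.95. Adjustment alone is therefore unlikely to rescue the efficacy claim.

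**Conclusion.** The concern holds in limited form. The Sample Size section credits the design with a property it lacks: about ±0.49 SD is too imprecise to estimate likely efficacy for planning. The Discussion also departs from Objectives and the design section on what feeds the main-trial calculation. If the observed effect were used, that trial could be badly mis-sized in either direction.

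The half-width rests on 64 completers split equally and independent outcomes. The main-trial sizes rest on assumed effects of 0.2 to 0.5 SD, because the article gives none. The target of 80 is not shown to be wrong and suits the feasibility and variability aims. Nothing in this trial's conduct has to change, so this is a clarification to make before the main trial is designed.

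**What to change.** Keep the target of 80.

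1. In Sample Size, remove the claim about likely efficacy and say whether 24-50 is per arm or in total.
2. Justify 80 by the precision it gives: about ±9 points on an 80% rate overall, about ±12 points per arm, and the pooled SD to about -15%/+21%.
3. Bring the Discussion into line with Objectives and the design section. The SD, the baseline-to-follow-up correlation (already planned in Statistical Data Analysis) and retention feed the main-trial calculation; the target difference is set independently of the observed pilot effect.

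Sizing the main trial on an upper confidence limit for the SD, such as the 80% limit at about 1.09 times the estimate, is optional.

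The cost is a few sentences and a more modest claim.

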#### Recruitment

Participants will be recruited from the Second Xiangya Hospital of Central South University through the following two ways: (A) Direct methods: access to research participants will be via two gatekeepers. The first gatekeeper will be the Director of the nursing department in the local hospital, who distribute the study information to the clinical departments managers on behalf of the researcher, (i.e., a communication message/talk based on the email/phone recruitment script). The second gatekeepers will be the clinical department managers who will help to identify the staff in service who are interested in participating and ask them to contact the researcher directly. (B) Indirect methods: Advertisement posters will be posted onto the hospital notice board and be disseminated via social media posts through individual WeChat moments. Participants who are interested in participating will be asked to contact the researchers via a dedicated email address, phone number, and WeChat message.

Once potential participants have expressed an interest in being involved, they will be assessed against the eligibility criteria by the researcher, and if they are eligible, they will then be asked if they have read the participant information sheet. Meanwhile, they will be given an opportunity to ask any questions, and if being addressed in satisfaction, they will be asked to give their written informed consent for participation in the trial. They will be asked to complete the baseline assessments and then randomization to either intervention or control group of the trial will occur.

#### Randomization

The randomization will be performed by an independent researcher not connected with either participant recruitment or data collection, using a 1:1 ratio as per a computer-generated randomization schedule using randomly permuted block sizes by randomization.com. All eligible participants who give written informed consent will be randomly allocated to either the intervention or control arm of the trial. Due to the nature of the study, only the researcher collecting/analyzing the data from trial participants can be masked to the randomization.

As a check on blindness, the researcher will be asked to guess the group allocation of trial participants after they have completed each final follow-up assessment. Unmasking will not occur until databases are closed and the main analysis has been completed.

### Intervention

#### Intervention

The whole process of this PFA training adaptation for delivery to Chinese frontline healthcare workers has been systematically described elsewhere. A detailed description of the Chinese ‘Preparing Me’ PFA training content has already been structured using the template for intervention description and replication checklist (TIDieR) in Table 1. Four trainers who have teaching and clinical psychological counseling background will be trained to deliver the PFA training intervention. Each of the six modules will be delivered in 75-min session blocks, incorporating didactic lectures, group exercises, role playing, and discussions to encourage active engagement and to improve the acquisition of PFA knowledge, skills, and techniques. All these sessions will be audio-recorded in preparation for the researchers to assess the fidelity using a PFA fidelity assessment tool. To support frontline healthcare participants to be able to apply the knowledge, skills, and techniques to their practice, two WeChat-based online supervision sessions will be offered.

#### Psychoeducation Programme (Control)

Participants in the control arm will receive the best available alternative to PFA training, which in this setting is the hospital's existing 1 day psychoeducation training course. This involves a series of lectures on basic mental health training topics, including the traditional Chinese culture, understanding psychological crisis and skills, referral resources, and ethics.

This study will attempt to minimize contamination between the two arms through (A) engaging different trainers with equivalent clinical and training experience to deliver the training; and (B) consenting participants in both arms will be asked not to share information regarding the training that they have received with colleagues who might be involved in a different arm of the trial.

### Secondary Objectives

The secondary objective (i.e., variability in participants outcomes) will collect two domains of measurement data that capture possible outcomes, mediator, moderator, or covariate to be included in any future effectiveness trial to quantitatively determine the acceptability and feasibility of randomized trial: (A) preparedness via knowledge, skills, and attitudes, and PFA practice in real setting; and (B) related psychological measures of resilience, self-efficacy, coping, post-event symptoms, post-traumatic growth, general health, and quality of life.

(A) Preparedness*Knowledge, Skills, Attitude*. The PFA Knowledge, Skills, and Attitudes Survey Form is a self-report, five-point Likert scale composed of 25 items organized by knowledge (10 items), skills (7 items), and attitudes (8 items) used to evaluate the learning effect of the PFA training intervention. It has been adapted from the Johns Hopkins PFA training initiative evaluation study and is empirically supported (44).*The PFA Training Follow-up Questionnaire*. It is an 11-item survey distributed to trainees twice, at 1- and 3-months after the training to determine the extent to which trainees have applied PFA knowledge and skills and their views on the acceptability and usefulness of PFA applied to persons who incurred crisis during a disaster event or other incident.(B) Related psychological measures*Brief Resilience Scale*. The Brief Resilience Scale consists of six items identifying one's ability to bounce back from stress developed by Smith {Smith, 2008 #15}. It is a five-point rating scale (1 = strongly disagree; 5 = strongly agree) and scored by reverse-coding Items 2, 4, and 6 and calculating the sum of all six items. This scale has established psychometric properties, exhibiting an acceptable internal consistency with Cronbach's α values equal to 0.76 and 0.72, respectively, in the Hong Kong and mainland samples (59, 60).*General Self-Efficacy Scale*. The General Self-Efficacy Scale (GSE) has become a widely used instrument for measuring general self-efficacy (61). The scale consisted of 10 items and each item was scored on a four-point Likert scale from 1 (strongly disagree) to 4 (strongly agree). The Chinese version of this scale has showed good reliability and validity in Chinese population (12).*The Impact of Event Scale-Revised*. The Impact of Event Scale-Revised will be used to determine the frequency of post-traumatic symptoms in relation to a recently experienced work-related traumatic event (62). It is a 22-item scale rated on a five-point Likert scale using anchors between 0 (not at all) to 4 (extremely) and total score range is 0–88 (higher score indicates greater severity). Good psychometric properties for the total scale and each subscale have been previously reported in Chinese sample (63).*The Simplified Coping Style Questionnaire*. The Simplified Coping Style Questionnaire (SCSQ) is used to assess the participants' attitudes and actions individuals that would take in the face of the life events (64). It is a 20-item self-report four-point Likert scales (0 = never; 3 = very often) that includes two dimensions: active coping (12-item) and passive coping (8-item). The instrument has demonstrated that the test–retest reliability coefficient of this instrument is 0.89, and Cronbach's α coefficient is 0.90 in Chinese populations (65).*Post-traumatic Growth Inventory*. The Posttraumatic Growth Inventory (PTGI) is developed to assess positive outcomes in response to traumatic events (66). The 21-item scale assesses positive psychological change in the wake of struggling with highly challenging event circumstances. Good psychometric properties of this instrument has been established in Chinese population (67).*General Health Questionnaire-12*. The General Health Questionnaire-12 is an 12-item self-report checklist devised by Goldberg is one of the most widely applied assessments of the severity of symptoms associated with psychological distress (68). The questionnaire contains 12 items, each scored on a four-point Likert scale from 0 to 3. The Chinese version shows a Cronbach's α coefficient was 0.86 for the overall GHQ-12 (69).*Professional Quality of Life*. The Professional Quality of Life Scale (ProQOL-5) is 10 items scale to assess one's perceived quality of life in relation to working as a helper and includes both the positive and negative aspects of this work (70). It is a five-point Likert self-reporting scale and consists of three components of professional QoL: compassion fatigue (CF), (BO, and compassion satisfaction (CS). The Cronbach's α coefficients for each dimension range from 0.758 to 0.821, and the test–retest reliability coefficients range from 0.764 to 0.867 (71).

### Data Collection

The schedule of enrolment, interventions, and assessments has been summarized in Figure 3. Demographic data will be recorded at baseline only, including age, gender, religion, marital status, living conditions, educational background, professional title, specialities, years of working experience, and experience of coping with crisis. Quantitative data will be collected from participants at three different times: baseline data will be collected before the PFA and psychoeducation training programmes (T0), the initial follow-up data will be collected immediately after training programmes are completion (T1), 1- and 3-months follow up data that will be followed up 1- and 3-months after the programmes are completed (T2, T3). The researcher will conduct data collection by providing each participant with a study pack at each time point. After presenting the information, the participants will be asked to complete these packs of assessment tools. To encourage participants' attendance at baseline and follow-up sessions, participants will be contacted by WeChat message at least 1 week before each data collection timepoint. The 1- and 3-months follow-up post-intervention measurement will be collected online via WeChat Wenjuanxing—a platform providing functions equivalent to Amazon Mechanical Turk. All questionnaires can be seen in Supplementary Materials.

**Figure 3 F3:**
[figure not shown]
Schedule of enrolment, interventions, and assessments.

### Statistical Data Analysis

Since this is a feasibility study and is not testing hypotheses regarding effectiveness of PFA training intervention, inferential statistics will not be employed. The primary objectives will be addressed via generating estimates of dispersion and central tendency (i.e., proportions, means, SDs, etc.). The acceptable levels of eligibility and enrolment will be a 90% or greater screening eligibility rate for frontline healthcare workers referred to the study. A recruitment rate is expected of 15 trainees per week and the target sample size would therefore be achieved in 6 weeks. The acceptable proportion of enrolled trainees who complete all the training sessions will be 80% or greater, given that there's 18% dropout rate of participants in PFA training cluster RCT (23). The feasibility of collecting quantitative outcome data includes (1) <20% missing data at the group level for each time point and (2) generating estimates of effect and variability related to by the independent research facilitator. Quantitative secondary objectives will be addressed via generating bivariate correlations and regression coefficients for the selected measures. Correlations between the baseline and follow-up will be estimated for continuous outcomes. Measures will be examined for multi-collinearity, as well as any needed transformation due to unfavorable skewness and kurtosis (72, 73). Appropriate 95% confidence intervals will be reported, with differences deemed significant at the 5% level.

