**Method:**

This is a two-armed feasibility randomized controlled trial (RCT) to be conducted among 80 Chinese frontline healthcare workers without prior related mental health training. Participants from the intervention group will receive an adapted PFA training program tailored to the Chinese frontline context to improve their knowledge and skills to support people in crisis. The primary objectives are to evaluate the training intervention's feasibility and the target population's acceptance of this educational intervention. The secondary objective is to obtain preliminary estimates of variability in participants' outcomes over a 3-months period. Measurements are taken pre-intervention (T0), post-intervention (T1), and at 1- and 3-months follow-up (T2–T3). A process evaluation using qualitative research with a subgroup of trainees, their clinical managers as well as trainers will be conducted to gain a comprehensive understanding of the intervention's acceptability and feasibility.

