**Primary objectives: Feasibility**			
1-1 Recruitment and retention	• Can numbers of frontline healthcare workers be adequately recruited, trained, and retained for outcome analyses?	• Process outputs: trainees (number available in wards, number at training, number at supervision sessions; number completing measurement tools and time 1, 2 and 3)	Trainees
1-2 Adherence	• How many participants attend training sessions/supervision sessions? • What are the reasons for failing to attend training and supervision sessions?	• Attendance record for training and supervision sessions • Observation fieldnotes of training and supervision sessions • Qualitative interviews with expert trainers, and trainees	Trainees, trainers
1-3 Feasibility of measurement tools	• Are the assessment tools acceptable to participants for collecting training outcomes? • Are the measurement tools sensitive to assess the changes?	• Measurement tools completion rate, time for completion, number of missing items • Qualitative interview with participants about appropriateness of outcomes measures	Trainees
1-4 Overtime changes	• Do healthcare trainees' knowledge, attitudes, skills, well-being change after training, and is this sustained at follow up?	• Outcome's assessment pre-and post- training, plus 1- and 3-months follow-up • Calculation with mean score and standard deviation over time	Trainees

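### The analysis section rules out inferential statistics and then sets a 5% significance rule for differences; the two statements cannot both be followed

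*Protocol article*

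**What the plan says.** The Statistical Data Analysis section begins: "Since this is a feasibility study and is not testing hypotheses regarding effectiveness of PFA training intervention, inferential statistics will not be employed". It then plans descriptive summaries, estimates of effect and variability, correlations and regression coefficients. Its last sentence is: "Appropriate 95% confidence intervals will be reported, with differences deemed significant at the 5% level". That sentence names no outcome, contrast, time point or test.

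The Sample Size section gives this basis: "A sample size of between 24 and 50 is considered reasonable in a feasibility study, to be able to estimate a participation rate". It sets a target of 80, "allowing for a 20% loss to follow-up rate and for at least 64 participants to complete the study during the COVID-19". It states no effect size, standard deviation or power, although it adds: "The sample size is projected to provide enough numbers to be able to estimate the likely efficacy and acceptability of the training intervention".

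The Secondary Objectives section describes nine instruments as candidate outcomes, mediators, moderators or covariates for a later effectiveness trial. The Discussion, under strengths, says that retention data, together with the training's ability to change the secondary measures, will shape that trial's design.

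**The concern.** An analyst cannot obey both the first and the last sentence of the paragraph. The last one licenses a significant or non-significant label on any difference the analyst chooses to compute, in a trial that was not sized for any comparison. Under such a rule some labels would be positive by chance, and others would be negative only because the trial is small.

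What is at stake is how the secondary measures are read. A chance-driven label could influence which measure is carried into the main trial, or be reported as evidence that the training does or does not work. If the contradiction is left standing, the choice of which sentence to follow could be made after the results are known.

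**Working it through.** **1. The two statements side by side.** The opening sentence excludes tests of effectiveness and all inferential statistics. The closing clause applies a 5% threshold to differences. The 95% confidence intervals are not the difficulty in themselves, since they suit a feasibility aim. Read literally, though, the opening sentence excludes intervals too, so it is broader than the rest of the paragraph can support. Restricting the 5% rule to the planned correlations and regression coefficients does not rescue it: the text speaks of differences, and tests of coefficients would be inferential as well.

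**2. The plan's own sample size.** 64 / (1 − 0.20) = 80, so the stated target reproduces. It is an attrition calculation. There is no power figure to reproduce.

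**3. What a 5% test could detect (illustration).**
- Inputs: 64 completers (Sample Size) and equal allocation, "using a 1:1 ratio as per a computer-generated randomization schedule" (Randomization), giving 64 / 2 = 32 per arm.
- Assumptions: the 5% level is two-sided, because it is paired with 95% intervals; SD = 1; effect sizes d are assumed, since the article gives none.
- The t statistic has noncentrality d × √(32/2) = 4d on 62 degrees of freedom.

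| True difference (SD) | Power, 32 per arm, unadjusted t-test |
|---|---|
| 0.2 | 12% |
| 0.3 | 22% |
| 0.5 | 50% |
| 0.8 | 88% |

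By the normal approximation, the difference detectable with 80% power is (1.96 + 0.84) × √(2/32) = 0.70 SD.

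The method matters. Adjusting for baseline with correlation r divides the effect by √(1 − r²). At 0.5 SD, power rises to about 62% for r = 0.5 and 79% for r = 0.7 (both r assumed). A within-arm change of 0.5 standardized units in 32 pairs has about 78% power.

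**4. How many labels the rule could reach (illustration).** Eight instruments could be scored at all three post-baseline times (T1, T2, T3). The follow-up questionnaire is given at two (1 and 3 months). With named subscales there are 13 scores: knowledge/skills/attitudes 3, resilience 1, self-efficacy 1, event impact 1, coping 2, growth 1, general health 1, professional quality of life 3.

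| Counting | Comparisons k | Expected false positives, 0.05k | Chance of at least one if independent, 1 − 0.95^k |
|---|---|---|---|
| 8 × 3 | 24 | 1.2 | 71% |
| 8 × 3 + 2 | 26 | 1.3 | 74% |
| 13 × 3 | 39 | 1.95 | 86% |
| 13 × 3 + 2 | 41 | 2.05 | 88% |

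These figures assume that every null is true and that every instrument is compared at each of its post-baseline times. The schedule figure is not shown, so the second assumption cannot be confirmed. Correlation between scores lowers the last column but not the expected count. With an assumed common correlation of 0.7, simulation gives about 32% for 26 comparisons and 38% for 41.

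**5. Interval width under the fix.** By the normal approximation, with 32 per arm, the 95% interval for an unadjusted between-arm difference has half-width 1.96 × √(2/32) = 0.49 SD.

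**The case against.** A reader might infer that the trial will issue significance claims across many outcomes. The document does not say that. The closing sentence specifies no outcome, contrast or test; it permits such claims without scheduling them. The counts of 24 to 41 comparisons are therefore illustrations. This objection stands.

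A reader might also take Table 2, item 1-4, as a second instance of the error, because it asks whether knowledge, attitudes, skills and "well-being change after training, and is this sustained at follow up". The method listed in that row is mean scores and standard deviations over time, which is already descriptive, so it is not a second instance.

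A third tempting reading is that the decision to proceed is at risk. It is not. The criteria in the analysis section concern eligibility (90%), recruitment (15 per week), completion of training (80%) and missing data (under 20%). The Conclusions tie the main trial to 80% retention. None of these uses a significance test.

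A fourth is that the protocol wrongly omits multiplicity control. A statistical analysis plan or full protocol may cover that and is not shown, so its absence here is no finding.

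Finally, the power figures of 50% and 22% are for an unadjusted comparison and improve with baseline adjustment. That is correct, and the range is given above. None of these objections reconciles the two sentences.

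**Conclusion.** The contradiction is explicit, lies within one paragraph and depends on no assumption. The consequence is limited: unpowered significance labels would be permitted on the secondary measures, and through the Discussion's stated use of those measures they could colour the design of the main trial. The primary feasibility objectives are untouched.

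The sizes in the working are illustrative. They rest on assumed effect sizes and on 32 completers per arm. The false-positive counts rest on all nulls being true and every instrument being compared at each of its post-baseline times. The point should be fixed, but it does not threaten the trial.

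**What to change.** - Delete the part of the closing sentence that follows the comma, which sets the 5% rule. Keep the 95% confidence intervals.
- Reword the opening sentence to say only that no hypothesis tests of effectiveness will be done. Without this change, interval estimates would still conflict with a blanket exclusion of inferential statistics.
- State that differences will be reported as estimates with 95% confidence intervals, without p-values or significance statements.

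Adjusting between-arm estimates for the T0 score, which is already collected, is an optional gain in precision and is not needed to resolve the contradiction.

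The cost is two edited sentences and one added. The sample size, visits and data collection do not change. The investigators give up only a claim that the paragraph's opening already disclaims. The edit should be made before the data are analysed.
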